### Statistical analysis

4.3

Data entry will be done independently by a clinic staff nurse and verified by another. Hardcopies of data collection forms and outcome measures will be kept in a locked safe, whereas softcopies are to be deposited at the repository center (Lab Archives), both at Monash University in Malaysia. Only the principal investigators ([name]), ([name]), and ([name]) have access to the interim results and makes the final decision to terminate the trial. The study team ensures that patients’ identity and personal information are coded to maintain confidentiality. In addition, ([name]) and the biostatistician ([name]), who will also be blinded, will conduct the statistical analysis by using International Business Machines Statistical Package for the Social Sciences (IBM SPSS; IBM Corp. Released 2013. IBM SPSS Statistics for Windows, Version 22.0. Armonk, NY) (v.22). The initial analysis will consist of descriptive statistics on demographic data, such as frequency distributions. Meanwhile the mean differences in primary and secondary outcomes are compared by using *t* tests or equivalent statistical method, whereas categorical outcomes are matched using chi square test. *P* values <.05 are considered statistically significant. Generalized mixed model analysis is adapted to investigate the variances between groups over time for all outcomes evaluated at the allocated time. Furthermore, the association between medication understanding and use self-efficacy, stroke knowledge, illness perception scores, as well as engagement in self-monitoring and clinic appointment attendance will be tested, as they seem to be critical indicators of behavioral changes. Multivariable analysis will be employed to examine the influence of the video narratives on stroke risk factor control and their covariates.^[61]^ Multiple imputation will be adapted to handle missing data if it occurs. In addition, withdrawn patients’ feedback about the intervention will be analyzed.

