### Sample size

2.3

A power analysis was carried out for an independent *t* test using the G∗Power version 3 to determine a sufficient sample size using an alpha of 0.05 and a power of 0.80.^[40]^ The estimation involved a medium effect size (*w* = 0.4) based on an average of effect sizes from similar recent studies associated to patient education in stroke, IMB, HBM, video narrative, and self-efficacy.^[25,41–43]^ However, sample size calculation according to stratification of stroke risk factors is not feasible because this is a disease with various underlying comorbidities and treatment heterogeneity. Thus, the desired sample size is 200 (100 each in intervention and control groups) are needed. With an estimated 15% attrition rate, 115 in each group will be recruited, thus yielding a target total sample size of 230.

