### Primary outcome measure

4.1

The primary outcome measure assessed at T0, T1, T2, T3, and T4 refers to medication understanding and use self-efficacy (MUSE).^[48]^ The study will observe the stage of medication usage behavior changes for each stroke preventative medication. MUSE with a scoring scale from 0 until 32 will be used to efficiently measure confidence in the understanding of individual's perceived ability using and adhering to the prescribed medicines, which differs from other medication-specific self-efficacy measures. Both the scales; learning and taking medication, have good internal consistency (Cronbach's alpha of 0.77 and 0.68) with acceptable construct validity and predictive validity. This scale has also been validated in the Malay language version.^[49]^

Knowledge and belief of the disease, as well as its preventative medication, have been associated with medication understanding and use self-efficacy. Therefore, the primary measures assessed at T0, T2, and T4 will also consist of validated Stroke knowledge test (SKT)^[50–52]^ and Brief illness perception questionnaire (BIPQ),^[53–55]^ whereby both have acceptable validity and reliability properties and available in the Malay language version. On top of that, this study will only adapt the BMQ specific Likert scale of the belief about medicine questionnaire^[56]^ so as to hinder redundancy and patient loading. This scale will be translated and validated in Malay language in a separate study. The SKT contains 20 questions with a scoring range of 0 to 20 regarding general information on stroke, such as pathophysiology, signs and symptoms, risk factors, and treatment methods and BIPQ, on the other hand uses a 0 to 10 scoring range of Likert-type scales for the general perception of one's illness. SKT measures differences in knowledge retention between groups whereby higher scores indicate better knowledge retention. BIPQ high scores reflect vulnerable thoughts of threatened attitudes about their disease, which will correlate to the impact of the intervention. Meanwhile, the BMQ specific is comprised of 2 scales; belief about the need of preventative medication (Necessity scale), and concerns about the potential adverse effect of the medication (Concerns scale). Higher scores indicate stronger beliefs about medicine usage.

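### No adjustment of MUSE for its own T0 score is named, so the planned t test, if it decides the trial, forgoes precision that is free to take

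*Protocol article*

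**What the plan says.** Section 4.3 (Statistical analysis) of the protocol article sets two methods for the primary outcome.

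- **Comparison of means.** "Meanwhile the mean differences in primary and secondary outcomes are compared by using" t tests or an equivalent method. No visit and no baseline adjustment are named.
- **Longitudinal model.** "Generalized mixed model analysis is adapted to investigate the variances between groups over time for all outcomes evaluated at the allocated time". Its terms, its contrast and its handling of T0 are not stated.

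Covariates are mentioned in 4.3 only for the multivariable analysis of stroke risk factor control, not for MUSE.

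Section 4.1 shows that the baseline score is available: "The primary outcome measure assessed at T0, T1, T2, T3, and T4 refers to medication understanding and use self-efficacy".

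Section 2.3 ties the size of the trial to the unadjusted test: "A power analysis was carried out for an independent" t test, "using an alpha of 0.05 and a power of 0.80".

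**The concern.** In a randomised trial with a continuous outcome also measured at baseline, adjusting the follow-up comparison for the baseline score removes the part of the outcome variance that baseline explains. It also corrects for chance imbalance in that score. An unadjusted t test at a follow-up visit does neither.

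The plan collects T0 MUSE in every patient but names no use of it in the comparison of MUSE between arms. The trial is sized to just reach 80% power with the unadjusted test, so any precision gained from T0 would be a real margin, for instance against a smaller effect than assumed. It needs no extra patient and no extra measurement.

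**Working it through.** **Inputs**

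- Test: independent t test (section 2.3).
- Alpha 0.05 and power 0.80 (section 2.3). Section 4.3 uses the same threshold: P "values <.05 are considered statistically significant". Sidedness is not stated.
- Effect size: "The estimation involved a medium effect size" of 0.4 (section 2.3). It is labelled *w* but is read here as the standardised mean difference *d*.
- Sample size: "the desired sample size is 200 (100 each in intervention and control groups) are needed" (section 2.3).
- Correlation ρ between T0 and follow-up MUSE: not given. **Assumed**, with a range of 0.2 to 0.7.

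**Step 1: reproduce the plan's figure.** For a two-sided t test with *n* per arm, power is the probability that a noncentral t variable with 2*n* − 2 degrees of freedom and noncentrality *d*√(*n*/2) exceeds the critical value in absolute size. With *d* = 0.4 and *n* = 100, the noncentrality is 0.4 × √50 = 2.83 on 198 degrees of freedom, and power is 0.8036. At *n* = 99 it is 0.7997, just short of 0.80, so 100 per arm is the smallest sufficient number and the stated 200 reproduces. Other readings do not fit: a one-sided test needs 78 per arm, and a chi-square test with *w* = 0.4 needs 50 in total.

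**Step 2: add baseline adjustment.** With T0 as covariate, the residual variance is multiplied by 1 − ρ², so the effective standardised difference is *d*/√(1 − ρ²). The same noncentral t calculation at 100 per arm gives the following (the one degree of freedom spent on the covariate is ignored):

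| Assumed ρ | 1 − ρ² | Effective *d* | Power | Gain over 0.8036 (points) | *n* per arm for 80% |
|---|---|---|---|---|---|
| 0.2 | 0.96 | 0.408 | 0.8193 | 1.6 | 96 |
| 0.3 | 0.91 | 0.419 | 0.8391 | 3.5 | 91 |
| 0.4 | 0.84 | 0.436 | 0.8667 | 6.3 | 84 |
| 0.5 | 0.75 | 0.462 | 0.9015 | 9.8 | 75 |
| 0.6 | 0.64 | 0.500 | 0.9404 | 13.7 | 64 |
| 0.7 | 0.51 | 0.560 | 0.9762 | 17.3 | 52 |

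At ρ = 0.5, the 25% fall in variance is worth an unadjusted trial of 100/0.75 = 133 per arm.

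**Step 3: why the model's handling of T0 matters.** Suppose a mixed model took T0 as one more outcome with separate baseline means per arm, and the contrast were the difference in change from T0 to one visit. The effective difference would then be *d*/√(2(1 − ρ)), and power would be 0.662, 0.804, 0.882 and 0.953 at ρ = 0.3, 0.5, 0.6 and 0.7. That is below the t test when ρ is under 0.5 and below baseline adjustment throughout, since 1 − ρ² = (1 − ρ)(1 + ρ) is less than 2(1 − ρ) for any ρ below 1. A mixed model that includes T0 with a common baseline mean recovers essentially what covariate adjustment gives. Section 4.3 does not say which form is meant, so these figures illustrate the range of specifications and do not describe the plan.

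**The case against.** The strongest reply is that nothing stated is invalid. An unadjusted t test in a randomised trial is unbiased, the sample size reproduces for it, and sizing on a t test is a normal, conservative choice. This stands: the point is one of efficiency, not of error or an undersized trial.

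Several stronger readings are tempting, and the article does not support them.

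- *That the unadjusted t test is the primary comparison.* Section 4.3 never calls it that and allows an equivalent method. Its link to the primary outcome comes through the sample size and the general sentence on means.
- *That about ten points of power are lost.* That needs ρ of about 0.5, which appears nowhere. Section 4.1 gives some reason for caution: it reports Cronbach's alpha of 0.77 and 0.68 for the two MUSE scales. Taking alpha as reliability, an observed ρ of 0.5 on a scale needs a true-score correlation of 0.5/0.77 = 0.65 or 0.5/0.68 = 0.74, over up to 12 months. No figure is given for the total score.
- *That the mixed model ignores baseline.* The text is silent, and the model covers all assessed visits, which for MUSE include T0. It may recover the information.
- *That naming two methods without ranking them is a contradiction.* A difference at a visit and a course over time can be separate questions, and the ranking may be settled in an analysis plan that is not shown. The point does not rest on this.

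It can also be said that section 2.1 calls the trial exploratory. That lowers the stakes, but the same section sets a primary aim of improvement over standard care, and section 2.3 powers a comparison for it.

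**Conclusion.** The point holds as a free improvement. The article names a t test for the primary outcome, sizes the trial on it, collects T0 MUSE, and names no adjustment of MUSE for that score. If the t test decides, power is 0.804 where an adjusted analysis of the same 100 per arm would have about 0.82 to 0.98, a gain of about 2 to 17 points for ρ from 0.2 to 0.7. If the mixed model decides and uses T0 well, little or nothing is lost.

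The size rests on *d* = 0.4, two-sided alpha 0.05, 100 analysable patients per arm, one follow-up visit and an assumed ρ. It also takes T0 MUSE to be unaffected by the intervention; section 3.1 places the first viewing after the outcome assessment. The direction does not depend on the value of ρ: apart from the degree of freedom spent, adjustment is no less precise than the unadjusted comparison.

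**What to change.** In section 4.3:

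1. Make the primary analysis of MUSE one linear mixed model over T1 to T4 with arm, visit, arm-by-visit and baseline MUSE (by visit) as covariate, in all randomised patients by assigned arm. An equivalent model that includes T0 as an outcome with a common baseline mean would serve as well.
2. Have the investigators name, before unblinding, the single visit or pooled contrast from this model that is the primary test. The article names none, so adjustment alone would not settle which result decides.
3. Use the same form for the other continuous outcomes measured at T0, each with its own baseline and its own visits. Section 4.2 lists quality of life only at T2 and T4, so it has no stated T0 score to adjust for.
4. Label the unadjusted t tests descriptive.

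The cost is one degree of freedom per baseline term and a few sentences. No new data are needed, the sample size can stay as it is, and the SPSS package already named can fit the model.

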## Discussion and conclusion

5

Persistent uncontrolled stroke risk factors can lead to unpredicted recurrent stroke event, thus making effective stroke preventive management a critical public health issue. The stroke care unit in Malaysia has limited patient education resources, especially for patients with medication understanding and use self-efficacy issues. The challenge is even higher for stroke patients who are affected by physical disability, thus hindering both motivation and self-independence. Various individuals’ illness beliefs and perceptions complicate one's thoughts towards definite health improvement and meaningful life. In such situation, the success of patient education strategies is at doubt. Patient education via video narratives has been found to be useful in primary care settings and other chronic disease clinic settings,^[32,33]^ but researches are in scarcity for effectiveness of video narrative at stroke care centers as part of the MTAC process.

As such, this study will determine if using doctor and patient video narrative could induce a positive behavioral change towards stroke risk control, whereby the initial observation should enhance medication understanding and use self-efficacy. Besides, the researcher believe that combining a doctor's perception of his stroke patients’ attitudes with a stroke patient's experiences about his or her stroke would deliver a mixed emotion of confidence and motivation towards self-efficacy. This idea, which is conceived from combined video narrative, refers to the effort to convey similar messages to stroke patients of varying learning styles and behavioral activation. This intervention is innovative as it combines health belief, motivation, and role model concept to trigger self-efficacy and self-responsibility to modify perceived negative lifestyle imbalances. Hence, it is foreseen that the discoveries from this translational research could serve as resources to further patient education development in stroke care settings. The researchers propose to share the findings to healthcare professionals and to the public via publication and conference proceedings.
